#### 4.4 Withdrawal of study subjects after study start/Discontinuation of Study Treatment

Subjects have the right to withdraw fully or partially from the study at any time and for any reason without prejudice to their future medical care by the physician or at the institution.

Withdrawal of full consent for a study means that the subject does not wish to receive further investigational treatment and does not wish or is unable to continue further study participation. Subject data up to withdrawal of consent will be included in the subject's study data, but no further information will be collected unless a separate consent has been given.

Withdrawal of partial consent means that the subject does not wish to take protocol-specific product(s) any longer but is still willing to collaborate in providing further data by continuing on study.

Should a subject request or decide to withdraw from the study, all efforts will be made to complete and report the observations as thoroughly as possible up to the end of withdrawal.

For any patient who has received IMP and withdrew prematurely from the study every effort should be made for attendance of a safety follow-up visit. The primary reason for withdrawal from the study should be documented. Patients will not be followed for any reason after consent has been withdrawn, unless a separate consent has been given for further data collection.

The investigator has the right to discontinue a patient from IMP or withdraw a patient from the study at any time. The primary reason for withdrawal from the study should be documented.

The investigator may withhold a participant from the boost shot if he/she experiences any of the following:

- becomes pregnant
- develops symptoms or conditions listed in the exclusion criteria
- experiences an AE after dosing that is considered by the investigator to be related to IP and is of Grade 3 (severe) or higher
- experiences an AE/SAE that, considered by the Investigator, requires IP withdrawal due to its nature, severity or required treatment, regardless of any causal relationship to vaccine

-shows a clinically significant vital sign measurement or finding on physical examination that, in the judgement of the investigator, requires IP withdrawal

If patient discontinues study participation for reasons unrelated to an adverse event, immunization of the patient will be continued according to the recommendations of the Austrian NIG (Nationales Impfgremium). No additional patient will be enrolled to replace that subject.

Reasons for removal investigational treatment or observation might include:

- Withdrawal of consent
- Administrative decision by the investigator
- Pregnancy
- Significant protocol deviation
- Subject noncompliance
- Serious Adverse event
- Other safety concern of the investigator or sponsor
- Death
- Lost to follow-up (participant repeatedly fails to return for scheduled visits without stating an intention to withdraw consent & he/she cannot be contacted by the study site after 3 contact attempts-these contact attempts must be documented in the participant`s medical record)

Participants that had been recruited during the first part of the study when this has still been conducted as a blinded and randomized study might request premature unblinding. In that case, participants might be kept part of the study after unblinding and will be further followed regarding durability of immune responses and breakthrough infections until day 180. If eligible, these participants might be included in a third vaccination.

## 5. Study Procedures

### 5.1 General Study Procedures and Assessments Schedule

The person obtaining consent must be suitably qualified and experienced, and have been delegated this duty by the CI/PI on the delegation log.

It is the responsibility of the investigator, or a person delegated by the investigator to obtain written informed consent from each subject prior to participation in the trial, following adequate explanation of the aims, methods, anticipated benefits and potential hazards of the study. The investigator or designee will explain the patients that they are under no

obligation to enter the trial and that they can withdraw at any time during the trial, without having to give a reason.

A copy of the signed informed consent form will be given to the participant. The original signed and dated form will be retained at the study site.

If new safety information results in significant changes in the risk/benefit assessment, the consent form will be reviewed and updated if necessary and subjects will be re-consented as appropriate.

## 5.2 Screening Visit (Day - 7 to -3)

All subjects must provide written informed consent before any study-specific assessments or procedures are performed.

Only subjects fulfilling all the inclusion and none of the exclusion criteria will be accepted in the study.

The following study screening assessments are to be completed prior to study entry:

- Physical examination including vital signs
- Pregnancy test (in case the previous test was performed more than 21 days before), in case of a positive pregnancy test the subject will be excluded from the study
- Blood draw:  
9 ml EDTA for antibody testing
- Concomitant medication
- Concomitant vaccination

Please note screening does not necessarily constitute enrolment. Screening failures i.e. patients who do not meet eligibility criteria at the time of screening may be eligible for rescreening at a later timepoint upon the decision of the Sponsor.

## 5.3 Visit I (Day 0, Day of Boost shot)

All subjects who have already received **ChAdOx1-S** as prime shot will receive the second dose with **Comirnaty (BNT162b2)**.

Subjects who have received **Comirnaty (BNT162b2)** as prime will be vaccinated again with **Comirnaty (BNT162b2)**.

Before IMP injection the following assessment should be performed:

- SARS-CoV-2 PCR Test (not older than 72 hours before vaccination)
- Alternatively: registered antigen test (not older than 24 hours before vaccination), participants will additionally give a sample for a PCR test at visit I prior to vaccination, in case this PCR test is positive the participant will be excluded after vaccination

After IMP injection AEs the subject will be observed for 30 minutes and all AEs/SAEs will be recorded.

Participants should seek immediate medical attention if they develop symptoms such as

- shortness of breath
- chest pain
- leg swelling
- persistent abdominal pain following vaccination
- neurological symptoms including severe or persistent headaches and blurred vision
- skin bruising (petechial) beyond the site of vaccination after a few days

#### 5.4 Visit III (Day 2 after boost shot)

The following assessments will be performed on Visit III:

- Physical examination including vital signs
- Blood draw
  - Coagulation (PT INR, antithrombin III, fibrinogen, D-Dimer, APTT)
  - CRP
  - Blood chemistry (albumin, alkaline phosphatase, aspartate aminotransferase (AST), alanine aminotransferase (ALT), lactate dehydrogenase (LDH), Gamma-GT, creatinine, uric acid, total bilirubin, total protein, blood urea nitrogen)
  - Hematology (Hematocrit, Hemoglobin, platelet count, WBC, RBC)
- AEs/SAEs
- Concomitant medication

## 5.5 Visit II, IV - VIII (Day 1, 3 – 7 after boost shot)

Subjects have to report information on reactogenicity on Day 1 and between Day 3 and Day 7 after boost shot. This information will be reported using an eDiary or via telephone call. The following information will be collected:

- pain at injection site
- erythema (redness) at injection site
- swelling/induration (hardness) at injection site
- localized axillary swelling or tenderness ipsilateral to the injection arm
- Headache
- Fatigue
- myalgia (muscle aches all over the body)
- arthralgia (aching in several joints)
- nausea/vomiting
- body temperature (potentially fever)
- chills
- other AEs

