| ediary, symptom reporting                             |                   |                                                      | x                                     |                                        | x                                                          |                                        |                                                                                |                                                            |

 Before vaccination;

 Assessment of antibody against wt and immune escape variants,

 Blood count, coagulation status, CRP, etc.

 Refer to COVID-19 disease observation schedule

 In case of positive Antigen-test

 Participants will be closely observed for at least 30 minutes post-vaccination to monitor for the development of acute reactions. Participants will be allowed to leave the study site after it is documented that the post-vaccination observation period is complete.

 not older than 72 hours before vaccination, alternatively: registered antigen test (not older than 24 hours before vaccination), participants will additionally give a sample for a PCR test at visit I prior to vaccination

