### 5.13 Visit II - VIII (Day 1 – 7 after 3rd vaccination)

Subjects have to report information on reactogenicity between Day 1 and Day 7 after 3rd vaccination. This information will be reported using an eDiary or via telephone call. The following information will be collected:

- pain at injection site
- erythema (redness) at injection site
- swelling/induration (hardness) at injection site
- localized axillary swelling or tenderness ipsilateral to the injection arm
- Headache
- Fatigue
- myalgia (muscle aches all over the body)
- arthralgia (aching in several joints)
- nausea/vomiting
- body temperature (potentially fever)
- chills
- other AEs

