## 7.9 Reporting Procedures

### 7.9.1 Reporting Procedures for Adverse Events (AEs)

A special section is designated to adverse events in the CRF where the following details must be entered:

- type of adverse event (diagnosis or syndrome; if not known signs or symptoms)

- start (date)
- end (date)
- severity (mild, moderate, severe, life-threatening/disabling, death)
- serious (no / yes)
- unexpected (no / yes)
- outcome (resolved, ongoing, ongoing – improved, ongoing – worsening)
- action taken (none, study medication dose reduced, study medication interrupted, study medication discontinued, medication therapy, surgical procedure, hospitalization, other)
- relation to study drug (possibly, probably or definitely related or unlikely, probably not related or definitely not related)

Certain events require immediate reporting to allow the sponsor to take appropriate measures to address potential new risks in a clinical trial. The investigator must report such events to the sponsor immediately; The reporting has to take place within 24 hours after notification. Regardless of relationship to study drug the investigator has to follow within 24 hours of notification:

- Serious adverse events
- Pregnancies

The investigator has to report immediately new significant follow-up information resulting from follow up examination to the sponsor (i.e. no more than 24 hours after becoming aware of the information). New significant information includes the following:

- new signs or symptoms or a change diagnosis
- new significant new diagnostic test results
- change in causality based on new information
- change in the event's outcome, including recovery
- additional narrative information on the clinical course of the event

Investigators must also comply with local requirements for reporting SAEs to the local health authority and IRB/EC

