### **Safety Analysis**

Safety evaluations will be based on the incidence, type, severity and consequences (e.g. study discontinuation) of an adverse event (AE) as well as on clinically significant changes in the patient's physical examination, vital signs, and clinical laboratory results (including immunotoxicity). Statistical analysis includes tabulation per treatment group using descriptive measures which are absolute and relative frequencies for categorical data and means, standard deviations, medians and interquartile ranges for continuous data. All safety analyses will be performed on the safety population.

All analyses will be performed in SPSS 26.0 or StataMP 16.0.

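### After the boost the named symptom list is not collected on Day 2, while after the third dose it runs on all of Days 1–7

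*Protocol*

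**What the plan says.** For the boost, Protocol section 5.5 reads: "Subjects have to report information on reactogenicity on Day 1 and between Day 3 and Day 7 after boost shot". The list has eleven named items (injection-site and axillary reactions, headache, fatigue, myalgia, arthralgia, nausea/vomiting, body temperature, chills) and a separate last entry for other AEs. It is filled in by eDiary or telephone.

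The boost visit plan says the same. Its row "ediary, symptom reporting" is marked for Visit II (Day 1) and Visits IV–VIII (Days 3–7), and is blank for Visit III (Day 2).

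Day 2 is a clinic visit. Section 5.4 opens with "The following assessments will be performed on Visit III" and then gives "Physical examination including vital signs", a blood draw, AEs/SAEs and concomitant medication. The named symptoms are not among them.

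For the third dose, section 5.13 says "Subjects have to report information on reactogenicity between Day 1 and Day 7 after" that vaccination, with the same list. There is no separate Day 2 clinic visit, and the third-dose visit plan marks the diary for the whole of Visits II–VIII.

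**The concern.** Secondary objective 2 in the Synopsis is a detailed analysis of safety and tolerability after the second vaccination, with emphasis on the heterologous arm. Secondary objective 4 covers the same ground for the third dose. Both rest largely on the daily symptom data.

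On Day 2 after the boost, collection changes from asking about each symptom by name to general AE recording. On Day 3 it changes back. Section 5.5 does not say that the Day 3 entry looks back to Day 2. A mild reaction that a participant would tick on a list may go unmentioned, or may not be judged worth an AE entry, when no list is used. After the third dose there is no such change.

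At stake is the completeness of the descriptive tolerability tables for one early post-boost day, and whether boost and third-dose daily symptom rates can be set side by side without a caveat. Section 1.4 invites that reading: it says no reactogenicity data exist for a third dose, and assumes that side effects of Comirnaty after two Vaxzevria doses will resemble those after one.

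**Working it through.** The protocol gives no figure on this point to reproduce, so the check compares the schedules and then the two ways of recording.

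**1. Schedules side by side**

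| | After the boost | After the third dose |
|---|---|---|
| Named symptom list, text | Day 1, Days 3–7 (section 5.5) | Days 1–7 (section 5.13) |
| Named symptom list, visit plan | Visit II, Visits IV–VIII; Visit III blank | Visits II–VIII |
| Day 2 contact | Clinic visit: examination, laboratory, AEs/SAEs, concomitant medication (section 5.4) | eDiary or telephone |
| AE row in visit plan, Days 1–7 | Marked throughout | Marked throughout |

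Text and table agree for both doses, so this is the plan as written and not a slip in one place.

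**2. Day count**

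- Named list after the boost: 1 + 5 = 6 of 7 days.
- Named list after the third dose: 7 of 7 days.
- Difference: 1/7 = 14% of diary days.
- Some form of AE collection: 7 of 7 days after both doses.

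**3. Is Day 2 AE recording the same as the list?**

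- Section 5.5 puts other AEs as a separate entry after the named symptoms, so the protocol itself treats the two as different.
- Section 7.2 defines an AE as an unfavourable change that the physician regards as clinically relevant. The list in section 5.5 has no such filter.
- Section 7.9.1 asks for start date, end date, severity and outcome, but only for events that have been entered as AEs.

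Day 2 AE recording is therefore not equivalent to solicited collection, and mild symptoms are where the two could diverge.

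**4. Which analyses are touched?**

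Section 11.3.5 plans safety descriptively: "Statistical analysis includes tabulation per treatment group using descriptive measures". Section 11.3.3 plans an individual-level comparison of second and third dose, but for efficacy. No formal comparison of reactogenicity between the doses is stated. The boost visit plan is common to all arms.

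**The case against.** The case for leaving the schedule alone is a good one. The diary skips Day 2 because the participant is in the clinic. The examination defined in section 5.10.1 covers skin, lymph nodes and the musculoskeletal system, which overlaps with several named symptoms. Section 7.9.2 requires all AEs, from participant or staff and whatever their cause, to be recorded during the first 7 days. Replacing a diary entry with a clinic visit is coherent. All of this stands, and it is why the point is small. It does not make the two methods equal, for the reasons in step 3 of the working.

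A reader might infer four stronger things that the documents do not support:

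- **Peak severity is lost.** The protocol does not say on which day reactions peak.
- **Duration cannot be calculated across Day 2.** Events entered as AEs carry start and end dates and a severity grade, whatever the diary days.
- **The two doses cannot be compared, or the boost will look milder.** Days 1 and 3–7 are collected alike, no reactogenicity comparison between doses is planned, and the direction of any bias is a possibility only.
- **One third of short reactions are missed.** That needs one-day symptoms spread evenly over Days 1–3 and no capture at Visit III. With an assumed capture share c at Visit III, the loss would be (1/3) × (1 − c): one third if c = 0, none if c = 1. The protocol gives neither the spread nor c.

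Nor is a bias between arms shown. Section 6.8 blinds participants only, while section 11.2 says investigators are blinded too. That conflict is a reason for care with clinician-recorded data, but the Day 2 schedule is the same in every arm.

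**Conclusion.** The point holds as a limited gap in data collection. The named symptom list misses one of seven days after the boost and none after the third dose. Day 2 after the boost is observed in person, but by a method that may record mild symptoms less completely, so the daily solicited data are not like-for-like between the two doses on that day.

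The consequence is confined to descriptive tolerability data under secondary objectives 2 and 4. The primary endpoint is not involved, and comparison between arms rests on a common schedule. The one assumption is that asking about symptoms by name captures mild reactions more fully than general AE recording. The wording of sections 5.5 and 7.2 makes this likely, but how much is missed cannot be calculated from the protocol.

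The change is worth making because it costs so little, not because a material loss has been demonstrated.

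**What to change.** Have the section 5.5 symptom list completed on Day 2 after the boost, either at Visit III or by eDiary. Amend three places so that they agree:

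- section 5.4: add the symptom list to the Visit III assessments;
- section 5.5: extend the reporting days to Days 1–7;
- the boost visit plan: mark Visit III in the eDiary row.

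For participants already past Day 2, state in the report that Day 2 was recorded by a different method. Restrict any descriptive boost-versus-third-dose comparison of solicited symptoms to Days 1 and 3–7.

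The cost is one more form entry at a visit that participants already attend, an eDiary setting and the amendment text. No visit or sample is added. The Synopsis plans up to 1000 participants in each of the two remaining arms, so those enrolled after the amendment would have the complete seven days.

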## 5.6 Visit IX (Day 10 ± 1 day)

The following assessments will be performed on Visit IX:

- Physical examination including vital signs
- Blood draw
  - Coagulation (PT INR, antithrombin III, fibrinogen, D-Dimer, APTT)
  - CRP
  - Blood chemistry (albumin, alkaline phosphatase, aspartate aminotransferase (AST), alanine aminotransferase (ALT), lactate dehydrogenase (LDH), Gamma-GT, creatinine, uric acid, total bilirubin, total protein, blood urea nitrogen)
  - Hematology (Hematocrit, Hemoglobin, platelet count, WBC, RBC)
- AEs/SAEs

- Immunogenicity blood draw:  
9 ml EDTA for antibody testing  
Up to 45 ml EDTA/heparin for T-cell analysis

### 5.7 Visit VIII, X – XXXIII (every 7 days $\pm$ 2 day after boost shot)

Every 7 days ( $\pm$  2) after boost shot until Day 182 subjects have to undergo antigen or RT-PCR testing. If this test confirms an infection with SARS-CoV-2, the clinical course and outcome will be followed. Virus from swabs will be isolated and sequenced and further analyzed for immune escape.

In addition, subjects complete their reports in the eDiary or via telephone call.

### 5.8 Additional visits on Day 30 (AV 1), Day 90 (AV 2) and Day 180 (AV 3) after boost shot ( $\pm$ 3 day)

The following examinations will be performed:

- Physical examination including vital signs
- Blood draw:  
9 ml EDTA for antibody testing  
Up to 45 ml EDTA/heparin for T-cell analysis
- Concomitant medication
- Concomitant vaccination
- AEs/SAEs

### 5.9 Unscheduled Visits

Unscheduled visits will not be integrated in the study except when they are related to a positive SARS-CoV-2 RT-PCR result or an adverse event.

### 5.10 Study Assessments

#### 5.10.1 Physical Examination

All physical examinations will be performed by trained medical personnel only.

A full physical examination including vital signs, height and BMI/weight (only at screening), will be performed according to the time points in the visit schedule. Symptom-directed physical examinations may be performed at other time-points at the discretion of the Investigator. The full examination includes assessment of skin, head, ears, eyes, nose, throat,

neck, thyroid, lungs, heart, cardiovascular, abdomen, lymph nodes and musculoskeletal system/extremities.

Heart rate and blood pressure will be measured after the patient has been in a sitting position for at least 5 minutes.

On Day0 vital sign measurements will be collected once before IP injection and 30 minutes after IP injection before participants are discharged from study site.

In case of blood collection, vital sign measurements should be performed before.

Febrile Participants at day 0 (body temperature  $\geq 38.0$  °C) may be rescheduled within the relevant window periods.

If any of the vital sign measurements is out of range and clinically significant at the discretion of the Investigator, the abnormal value will be documented on the AE page of the eCRF.

#### 5.10.2 SARS-CoV-2 RT-PCR-testing

Weekly antigen or RT-PCR tests have to be performed starting on Day 7 until Day 182 after boost shot.

#### 5.10.3 Surveillance of clinical course and outcome of SARS-CoV2 infection

In case of a positive SARS-CoV-2 RT-PCR test the subject will be followed until end of quarantine and full recovery.

The following information will be collected for subjects in outpatient care:

- Fever (temperature  $\geq 38^{\circ}\text{C}$ ) or chills (of any duration, including  $\leq 48$  hours)
- Shortness of breath or difficulty breathing (of any duration, including  $\leq 48$  hours)
- Cough (of any duration, including  $\leq 48$  hours)
- Fatigue
- Muscle or body aches
- Headache
- New loss of taste or smell
- Sore throat
- Congestion or runny nose
- Nausea or vomiting
- Diarrhea
- Symptoms of long-Covid

Additional information must be collected for hospitalized subjects and infection will be defined according to the WHO score for COVID-19 (ordinal scale for Clinical Improvement)

- Clinical signs indicative of severe systemic illness, Respiratory Rate  $\geq 30$  per minute, Heart Rate  $\geq 125$  beats per minute, SpO2  $\leq 93\%$  on room air at sea level or PaO2/FIO2  $< 300$  mm Hg, OR
- Respiratory failure or Acute Respiratory Distress Syndrome (ARDS), (defined as needing high-flow oxygen, non-invasive or mechanical ventilation, or ECMO), evidence of shock (systolic blood pressure  $< 90$  mmHg, diastolic BP  $< 60$  mmHg or requiring vasopressors), OR
- Significant acute renal, hepatic or neurologic dysfunction, OR
- Admission to an intensive care unit or death

